### 11.2.1 Sample Size Assumptions

The sample size calculation is based on the primary endpoint, the 1-year cumulative incidence of relapse post-transplantation, with the following assumptions:

- - - - the 1-year cumulative incidence of relapse in the control group: 40%
      - the 1-year cumulative incidence of relapse in the sorafenib group: 20%
      - a 1:1 randomization scheme
      - a 5% one-tailed risk of erroneously claiming a difference in the presence of no true underlying difference by z-test with pooled variance
      - a 90% chance of successfully declaring a difference in the presence of a true underlying difference (power)
      - 10% percent of cases drop

Under the above assumptions, a total sample size of 194 subjects is required (97 in each group).

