| **Study treatment** | **Sorafenib maintenance**  For subjects randomized to sorafenib maintenance (sorafenib group), sorafenib is started from day +30 until day +180 post-transplantation if patients meet the inclusion criterion on day +30. For patients who do not meet the inclusion criterion on day +30 but who do so within 31-60 days post-transplantation, sorafenib is administrated at 31-60 days post-transplantation and continued until day +180. The initial dose of sorafenib is 400 mg orally twice daily (BID). In cases of grade 3 or worse AEs, dose modifications including dose reductions or interruptions are allowed at the investigator’s discretion. After the resolution of AEs, the dose is re-escalated from 200 mg once every day or 200 mg BID to 400 mg BID.  **Non-maintenance**  For subjects randomized to non-maintenance (control group), neither sorafenib nor other FLT3 inhibitors are used unless the patients experience relapse. |
| **Sample size determination** | This trial is designed to test the hypothesis that sorafenib maintenance post-transplantation is superior to non-maintenance post-transplantation with respect to relapse. The sample size calculation is based on the primary endpoint, the 1-year cumulative incidence of relapse, which is approximately 40% in the patients with FLT3-ITD AML undergoing allo-HSCT with non-maintenance post-transplantation. To identify a 20% absolute decrease in the 1-year cumulative incidence of relapse with sorafenib maintenance post-transplantation, a minimum of 176 patients (88 in each group) is required to provide the study with a significance level of 0.05 and a power of 90%. After adjusting for a 10% dropout, the total planned sample size is 194 patients (97 in each group). |

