# 11. Data Analysis and Statistical Considerations

## 11.1. Hypotheses

The primary endpoint is the 1-year cumulative incidence of relapse post-transplantation. The null and alternative hypotheses are designed with the goal of demonstrating the superiority of sorafenib maintenance over non-maintenance post-transplantation with respect to relapse. Superiority will be determined using the following hypothesis:

H0: incidence of relapse with sorafenib maintenance ≥ incidence of relapse with non-maintenance post-transplantation

H1: incidence of relapse with sorafenib maintenance < incidence of relapse with non-maintenance post-transplantation

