### 11.3.2.2 Analysis of Efficacy

The definition of efficacy endpoints has been detailed in previous section. Cumulative incidence of relapse post-transplantation is calculated by accounting for competing risk. Non-relapse mortality is considered a competing risk for relapse. The comparison of the cumulative incidence of relapse is tested using Fine and Gray model. OS and LFS are estimated using the Kaplan-Meier method and compared using the log-rank test. The corresponding HR and 95% CI were estimated using the Cox proportional hazards model. All statistical tests are two-tailed with a significance level of 0.05. SPSS 20.0 (SPSS Inc., Chicago, IL, USA) and R version 3.3.0 (R Development Core Team, Vienna, Austria) are used for all data analysis.

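### The sample size assumes a one-tailed 5% test but all analyses are two-tailed at 0.05, so the stated 90% power is about 83% on the protocol's own method

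*Protocol*

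**What the plan says.** Four places in the protocol bear on the error rate of the primary comparison.

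- **Section 11.2.1, Sample Size Assumptions** takes "a 5% one-tailed risk of erroneously claiming a difference in the presence of no true underlying difference by z-test with pooled variance". The other inputs are control relapse of 40%, sorafenib relapse of 20%, 1:1 allocation, 90% power and 10% dropout. The result is 194 patients, 97 per group.
- **Study Synopsis, Sample size determination** gives the step before dropout, 176 patients or 88 per group, which "is required to provide the study with a significance level of 0.05 and a power of 90" per cent. It does not say whether the 0.05 is one- or two-tailed.
- **Section 11.1, Hypotheses** is one-directional: "H1: incidence of relapse with sorafenib maintenance < incidence of relapse with non-maintenance post-transplantation". It gives no significance level.
- **Section 11.3.2.2, Analysis of Efficacy** names the Fine and Gray model for relapse and then says, in the same paragraph: "All statistical tests are two-tailed with a significance level of 0.05".

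**The concern.** The calculation and the analysis use different critical values: 1.645 for the sample size and 1.960 for the test. Power of 90% computed with the first does not carry over to the second. A reader of the synopsis alone cannot see this, because the tail is not named there.

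Two things are at stake. First, the trial is more likely than stated to miss the 20-point reduction that section 11.2 calls clinically meaningful. Second, a one-sided p-value between 0.025 and 0.05 would count as success by the rule in section 11.2.1 and as failure by the rule in section 11.3.2.2. The chance of a false claim in favour of sorafenib is 5% under the first and 2.5% under the second. In an open-label trial that choice should not remain open once results are known.

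**Working it through.** **Inputs** (section 11.2.1 unless noted): p₁ = 0.40, p₂ = 0.20, equal groups, power 0.90, pooled-variance z-test, alpha 0.05 one-tailed; 88 per group before dropout (synopsis); alpha 0.05 two-tailed for the analysis (section 11.3.2.2).

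The mean proportion is 0.30. The null term is √(2 × 0.30 × 0.70) = √0.42 = 0.6481. The alternative term is √(0.40 × 0.60 + 0.20 × 0.80) = √0.40 = 0.6325.

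**Step 1. Reproduce the protocol's figure.**

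n per group = [z_α × 0.6481 + 1.2816 × 0.6325]² / 0.20²

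- One-tailed, z_α = 1.645: (1.0660 + 0.8105)² / 0.04 = 88.03. This is the protocol's 88 (strictly, rounding up gives 89). Power at 88 is 89.99%.
- Dropout: 88 × 1.1 = 96.8, rounded up to 97. This matches.

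**Step 2. Could 88 come from a two-tailed calculation?** No two-tailed variant tried gives it:

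| Method, 90% power | One-tailed, per group | Two-tailed, per group |
| --- | --- | --- |
| Unpooled z-test | 86 | 106 |
| Arcsine | 88 | 108 |
| Pooled z-test | 89 (88.03) | 109 (108.2) |
| Continuity-corrected | 98 | 119 |

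The one-tailed wording is therefore not a slip of the pen over a two-tailed computation; the number depends on it.

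**Step 3. Power under the two-tailed rule.**

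power = Φ[(0.20 × √n − 1.960 × 0.6481) / 0.6325]

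- n = 88: (1.8762 − 1.2702) / 0.6325 = 0.958, power **83.1%**. The miss rate is 1 − 0.831 = 16.9%, against 10% stated.
- n = 97 (no dropout at all): (1.9698 − 1.2702) / 0.6325 = 1.106, power **86.6%**.

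**Step 4. Difference detectable with 90% power, two-tailed, 88 per group.** For 40% against 18%, the mean is 0.29, the null term √0.4118 = 0.6417 and the alternative term √0.3876 = 0.6226. Then (0.22 × 9.3808 − 1.960 × 0.6417) / 0.6226 = 1.295, power 90.2%. The detectable difference is about 22 points, not 20.

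**Step 5. Approximation closer to the planned test.** Assume proportional subdistribution hazards and 1-year follow-up for everyone. The subdistribution hazard ratio is ln 0.80 / ln 0.60 = 0.437, with |ln| = 0.828. Expected relapses are n per group × (0.40 + 0.20). Power is Φ(√events / 2 × 0.828 − z_α).

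| Patients | Relapses | One-tailed power | Two-tailed power |
| --- | --- | --- | --- |
| 176 | 52.8 | 91.4% | 85.3% |
| 194 | 58.2 | 93.5% | 88.5% |

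Two-tailed 90% power needs 4 × (1.960 + 1.2816)² / 0.828² ≈ 61.3, so 62 relapses.

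**Step 6. Other two-tailed checks at 88 per group.** Exact binomial power of the pooled z-test is 83.8%, unpooled 84.3%, continuity-corrected 78.5%.

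**The case against.** The strongest reply is that 83% sits towards the low end and is not the power of the test that will be run. The primary test is Fine and Gray, for which the approximation gives 85.3% to 88.5%. The intention-to-treat population is everyone randomized, withdrawn patients stay in follow-up unless they withdraw consent (sections 4.2 and 9.1), and a censored analysis uses their time up to loss. The real shortfall may then be only 2 to 7 points.

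This stands as a refinement: the honest statement is a range that names its method. It does not rescue the 90%. The protocol's own 90% was computed with the z-test and 88 per group, so 83% is the like-for-like comparison. Changing to the event-based method raises the one-tailed figure too (91.4%), and the loss from going two-tailed is about the same: 91.4 − 85.3 = 6.1 points, against 90.0 − 83.1 = 6.9. Even with no dropout, no version reaches 90%.

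A second reply is that only section 11.3.2.2 governs the analysis. On that view the one-tailed 5% is just a planning assumption, and a directional hypothesis tested two-tailed is ordinary practice. Much of this is fair. Read strictly, section 11.3.2.2 holds the risk of falsely favouring sorafenib at 2.5%, and the direction in section 11.1 is not itself an error. But section 11.2.1 describes its one-tailed 5% as the risk of wrongly claiming a difference, which is a statement about the decision, and the protocol does not say which statement prevails. The certain harm is the overstated power; the double threshold is an ambiguity to close.

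The absence of the statistical analysis plan does not matter here. The protocol has already fixed the tail in two incompatible ways.

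**Conclusion.** The concern holds. The sample size belongs to a one-tailed 5% test, and the analysis section prescribes a two-tailed 5% test. On the protocol's own method the power is about 83%, not 90%, if the 10% dropout occurs in full, and about 87% if nobody is lost. Allowing for the planned Fine and Gray analysis, the reasonable span is about 83% to 88%. These figures take the 40% and 20% relapse assumptions as given. The Fine and Gray figures also rest on proportional subdistribution hazards and complete 1-year follow-up.

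**What to change.** Keep the two-tailed 0.05 test of section 11.3.2.2, which is the stricter rule, and bring the planning text into line with it.

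1. In section 11.2.1, delete the one-tailed statement. In section 11.2.1 and the synopsis, restate the power, for example: *At two-tailed 0.05, for relapse of 40% against 20%, a pooled z-test has about 83% power with 176 patients contributing 1-year outcomes and about 87% with all 194. With 176 patients it has 90% power for 40% against 18%. The corresponding approximations for the Fine and Gray analysis are about 85% and 88% for 40% against 20%.*
2. In the synopsis, state that the 0.05 is two-tailed.
3. Optionally, write section 11.1 as a two-sided hypothesis, so that there is visibly one decision rule.

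The cost is wording in three places and a less favourable stated power; no patients are added. If the sponsor wants to keep 90% power with the two-tailed test, 109 per group are needed before dropout. That is 120 per group (240) with the protocol's × 1.1 inflation, or 122 per group (244) when dividing by 0.9, so 46 to 50 more patients than the planned 194. Declaring the primary test one-tailed at 0.05 would also restore 90%, but it would double the risk of a false claim of benefit from 2.5% to 5%, so it is the weaker choice.

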### 11.2.2 Primary Efficacy Endpoint

The primary efficacy endpoint is the 1-year cumulative incidence of relapse post-transplantation.

### 11.2.3 Secondary Efficacy Endpoints

The secondary efficacy endpoints include OS and LFS.

## 11.3 Data Analysis Considerations

### 11.3.1 Analysis Population

The primary population will be the intent-to-treat (ITT) population, which is defined as all subjects randomized to the two groups. This ITT population will be the basis for the analysis of efficacy and safety endpoints in this study.

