# 3. Study Design

This is a prospective, open-label, multicenter, randomized, phase 3 study of comparison of sorafenib maintenance versus non-maintenance post-transplantation in patients with FLT3-ITD AML undergoing allo-HSCT. The study design is illustrated in Figure 1.

Subjects with FLT3-ITD AML receiving first allo-HSCT will be screened for eligibility. Medical history evaluation, vital sign, physical examination, Eastern Cooperative Oncology Group (ECOG) performance status, blood and urine sampling for laboratory tests, electrocardiogram, chest imaging examination as well as bone marrow (BM) assessment will be performed to determine study eligibility, all of which must be performed ≤3 days prior to randomization. Eligible subjects will be randomized in a 1:1 ratio to receive sorafenib maintenance or non-maintenance post-transplantation. Randomization is performed with randomization codes generated by a computer-generated randomization system.

Based on the randomization and assignment, the subjects will receive sorafenib maintenance or non-maintenance post-transplantation. For subjects in the experimental intervention arm (sorafenib group), sorafenib is started from day +30 until day +180 post-transplantation if patients meet the inclusion criterion on day +30. For patients who do not meet the inclusion criterion on day +30 but who do so within 31-60 days post-transplantation, sorafenib is administrated at 31-60 days post-transplantation and continued until day +180. The initial dose of sorafenib is 400 mg orally twice daily (BID). In cases of grade 3 or worse AEs, dose modifications including dose reductions or interruptions are allowed at the investigator’s discretion. After the resolution of AEs, the dose is re-escalated from 200 mg once every day (QD) or 200 mg BID to 400 mg BID at the discretion of the investigator. For subjects in the no intervention arm (non-maintenance, control group), neither sorafenib nor other FLT3 inhibitors are used unless the patients experience relapse. No crossover between the two groups before relapse will be allowed.

Disease assessment including routine blood and BM assessment will be regularly performed post-transplantation. BM assessment, including BM smear and FLT3-ITD mutation is performed before randomization, every month for the first three months after enrollment, every two months from the 4th to 9th month after enrollment, and then every three months until the study is completed.

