## 5.3.2 Control Group (non-maintenance therapy)

Neither sorafenib nor other FLT3 inhibitors can be used unless the patients experience relapse.

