### 8.1. Definitions

## 8.1.1 Adverse Events

An AE is any untoward medical occurrence in a subject of a clinical investigation, which does not necessarily have a causal relationship to the medicinal product. Therefore, an AE can be any unfavorable and unintended sign, including an abnormal laboratory finding, symptom, or disease (new or exacerbated), whether or not it is considered to be related to the product. This definition includes any newly occurring event or previous condition that has increased in severity or frequency since the administration of the product. However, relapse or death due to relapse should not be recorded as AEs.

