### 11.3.2.3 Analysis of Safety

Safety and tolerability will be assessed by incidence and severity of AEs and changes from baseline of all relevant parameters, including laboratory test values, physical examination, vital signs, and ECOG performance scores. The definition of AEs has been detailed in previous section. With the exception of GVHD and hematologic AEs, all AEs are graded according to CTCAE version 4.0. aGVHD, cGVHD, and hematologic AEs are graded as AEs according to our self-defined criteria. All subjects will be monitored for AEs within 210 days post-transplantation. Categorical data will be summarized by proportion of total subjects. Quantitative data will be described using arithmetic average or median for central tendency and standard deviation or interquartile range for distribution range.

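### Safety is summarised only by randomised arm, as crude proportions to day 210 with no cut at relapse, so post-relapse toxicity falls mainly on the control arm

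*Protocol*

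**What the plan says.** The protocol fixes the following.

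- **Population (11.3.1).** The ITT set, "which is defined as all subjects randomized to the two groups", serves both purposes: "This ITT population will be the basis for the analysis of efficacy and safety endpoints in this study". No other safety set is defined.
- **Window (11.3.2.3, also sections 3 and 5.4).** "All subjects will be monitored for AEs within 210 days post-transplantation". No cut-off at relapse or at the start of later therapy is given.
- **Summary measure (11.3.2.3).** "Categorical data will be summarized by proportion of total subjects".
- **Control arm (5.3.2).** "Neither sorafenib nor other FLT3 inhibitors can be used unless the patients experience relapse". Section 3 matches: "No crossover between the two groups before relapse will be allowed".
- **What is recorded.** Section 8.4 calls for every AE and SAE whatever its cause. The only relapse-related exclusion is in 8.1.1: "However, relapse or death due to relapse should not be recorded as AEs".

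**The concern.** Each rule is ordinary taken alone. Together they mean that a control who relapses on, say, day 120 and then starts sorafenib or salvage therapy has the resulting toxicity counted as an AE of the no-sorafenib arm. The same happens to sorafenib patients who relapse, but the design expects half as many of them. The contamination is therefore differential, and it grows with efficacy: the better sorafenib prevents relapse, the worse the control arm's AE profile looks beside it.

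Tolerability is in the trial's title and comparing AEs is a secondary objective (2.2). Section 7.3 also raises a possible increase in GVHD with sorafenib. A comparison that understates excess toxicity bears on one of the trial's main outputs.

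**Working it through.** **Inputs from the protocol.** One-year relapse of 40% in controls and 20% with sorafenib (11.2.1); 97 patients per arm (4.1.1); start of sorafenib between days 30 and 60 (5.3.1); AE window to day 210.

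**The plan's own figure.** A one-sided 5% pooled z-test with 90% power for 40% v 20% gives 89 per arm against the stated 88 (power at 88 is 0.8999). Then 88 × 1.10 = 96.8, or 97. The denominator reproduces closely, and the point does not depend on it. The plan gives no figure for safety.

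**Step 1: relapse before day 210.** The timing of relapse within the year is not stated, so it is varied. Competing death is ignored.

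Constant hazard from day d, scaled to reach p at day 365: F = 1 − exp[ln(1 − p) × (210 − d)/(365 − d)]. Linear rise: F = p × (210 − d)/(365 − d).

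| Assumption | Control, of 97 | Sorafenib, of 97 |
|---|---|---|
| Constant hazard, d = 0 | 25.5% (24.7) | 12.0% (11.7) |
| Constant hazard, d = 30 | 24.0% (23.3) | 11.3% (11.0) |
| Constant hazard, d = 60 | 22.2% (21.5) | 10.4% (10.1) |
| Linear, d = 0 | 23.0% (22.3) | 11.5% (11.2) |
| Linear, d = 30 | 21.5% (20.8) | 10.7% (10.4) |
| Linear, d = 60 | 19.7% (19.1) | 9.8% (9.5) |

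A further version takes annual hazards of −ln(0.6) = 0.511 and −ln(0.8) = 0.223 from transplantation and follows patients still relapse-free at day 45:

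- control: 1 − exp(−0.511 × 165/365) = 0.206, or 20.0 of 97;
- sorafenib: 1 − exp(−0.223 × 165/365) = 0.096, or 9.3 of 97.

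Overall this is 19-25 controls and 9-12 sorafenib patients, a ratio of 2.0 to 2.2.

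**Step 2: time at risk.** With a constant hazard from day 30 or 60, the share of the window to day 210 that lies after relapse is 12.5% or 11.6% in controls and 5.8% or 5.3% with sorafenib.

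**Step 3: effect on the proportion with a grade 3 or worse AE.** Assume the same background risk b in both arms, so no true difference. Let a share q of relapsed patients then have such an event, independently of the background. The observed proportion is b + q × r × (1 − b), where r is the proportion relapsed. The shift between arms is q × (r_control − r_sorafenib) × (1 − b).

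With r = 0.206 and 0.096 and q = 1:

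- b = 0.3: 44.4% v 36.7%, shift 7.7 points;
- b = 0.4: 52.4% v 45.8%, shift 6.6 points;
- b = 0.5: 60.3% v 54.8%, shift 5.5 points.

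With q = 0.5 the shift is 2.8-3.9 points. These r values imply one-year relapse after day 45 of about 36% and 18%. Rescaling to 40% and 20% gives r = 0.232 and 0.109, and shifts of 6.1-8.6 (q = 1) or 3.1-4.3 (q = 0.5). Over every row of the table the range is 4.9-9.4 (q = 1) or 2.5-4.7 (q = 0.5).

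**Step 4: sorafenib given to relapsed controls.** Assume an AE risk of 10% off drug and 30% on drug, 20-25% of controls relapsed, and 50-100% of those given sorafenib. Control risk then reads between 0.10 + 0.20 × 0.5 × 0.20 = 12% and 0.10 + 0.25 × 1 × 0.20 = 15%. A true excess of 20 points reads as 15-18. The sorafenib arm is held at 30% here.

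**The case against.** Several counter-arguments have force.

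- **Counting after relapse is inferred.** No sentence says it. It follows from following all subjects with no cut-off. Section 4.2 allows withdrawal for starting other FLT3 inhibitors and 9.1 for treatment failure; follow-up after withdrawal is then described for the disease, not for AEs. Some post-relapse events may go uncollected. This stands, but discretionary loss is not a remedy, and sorafenib itself is not among the other inhibitors named in 4.2.
- **An SAP may refine the analysis.** True of treatment-emergent rules and exposure adjustment. But the protocol itself fixes the population and the crude denominator.
- **Mitigating text exists.** Relapse and death from relapse are not AEs, and 8.3 requires a causality judgement for each event. The first does not remove the toxicity of later therapy. The second is not used in 11.3.2.3 to separate events.
- **Counting by arm over a common window is a legitimate treatment-policy summary.** It is, and it should stay. A summary cut at relapse has its own fault: unequal time at risk.
- **The effect is modest.** Taking q = 1 is extreme, above all for relapses shortly before day 210. Even the full shift lies inside the 95% half-width for a difference at 97 per arm, about 14 points: 1.96 × √(2 × 0.4 × 0.6/97) = 0.138. But the shift is systematic, which that imprecision does not excuse.

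Two stronger readings may tempt a reader. One is that 8.1.1 leaves controls without an AE baseline because it mentions a "previous condition that has increased in severity or frequency since the administration of the product". That clause adds to a general definition covering any trial subject, and 10.1 starts follow-up at randomisation, so the reading fails. The other is that never-dosed patients materially dilute the sorafenib arm. Eligibility is confirmed within three days before randomisation and nothing in the documents quantifies non-dosing; the effect is probably small.

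**Conclusion.** The point holds as a directional weakness in the only stated safety analysis. On the plan's own relapse assumptions, post-relapse toxicity enters the control arm about twice as often as the sorafenib arm, which understates the excess toxicity of sorafenib. That direction requires only that relapse be commoner in controls and that post-relapse therapy add AEs before day 210.

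The size is illustrative: about 3-4 points with half of relapsed patients affected, and 5.5-7.7 as the upper bound with all affected, for the day-45 relapse figures. Other relapse timings move these by one or two points. Background risk, the share affected and the use of sorafenib after relapse are all assumptions.

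The documents do not support concluding that the ITT safety summary is invalid or should be replaced by an as-treated comparison. It answers one question; a second summary is needed to show tolerability of maintenance while patients remain in remission.

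**What to change.** Keep the ITT summary by arm. In 11.3.1 and 11.3.2.3:

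1. Add a summary by randomised arm of AEs from randomisation to the earliest of relapse, death or day 210, given as rates per patient-month and as cumulative incidence with relapse and death as competing events.
2. Report AEs after relapse separately by arm.
3. Add a sensitivity summary restricted, in the sorafenib arm, to patients who took at least one dose. List never-dosed patients; do not move them to control.

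Section 8.1.1 needs no change. Treatment, visits and sample size are untouched.

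The cost is a little more programming. The pre-relapse summary has shorter and unequal time at risk, which is why the rates and the retained ITT summary belong beside it. AE onset dates must be on the CRF; the protocol does not confirm that they are, so this should be checked first.
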